## Abstract

**Background:**

Nonalcoholic fatty liver disease (NAFLD) is one of the most common chronic liver diseases worldwide. Evidence showed that anthocyanins might have effects on NAFLD. Protective effects of Cornelian cherry (*Cornus mas* L.) extract, as an anthocyanins-rich source, on liver were reported in animal studies. However, very few clinical trials were conducted in this regard. Thus, the aim of this research will be to evaluate the effect of supplementation with total anthocyanin-base standardized cornelian cherry fruit extract on liver function (Serum levels of Alanine aminotransferase (ALT), Aspartate aminotransferase (AST), cytokeratin-18 fragment M30 (CK-18 M30), as well as steatosis and fibrosis of liver), tumor necrosis factor α (TNF-α), malondealdehyde (MDA), and adiponectin in patients with NAFLD.

**Methods:**

In a double-blind randomized clinical trial, 80 NAFLD patients will be studied. The patients will be randomly assigned into two groups. The intervention group will receive the cornelian cherry extract, containing 320 mg.d^− 1^ anthocyanins, per day for 12 weeks. The control group will also take the placebo daily for 12 weeks. Liver function (Serum levels of AST, ALT and CK-18 M30; steatosis and fibrosis of liver), serum levels of TNF-α, MDA, and adiponectin will be measured at the baseline and the end of trial for both groups and their results will be compared.

**Discussion:**

Considering evidences about the useful impacts of anthocyanins on NAFLD, the effects of supplementation with cornelian cherry extract will be investigated on the important variables related to NAFLD.

**Trial registration:**

Iranian Registry of Clinical Trials (IRCT20180419039359N1).

## Background

Nonalcoholic fatty liver disease (NAFLD) is one of the most prevalent chronic liver diseases [1–4]. The overall prevalence of NAFLD was from 5 to 20% among the healthy populations and more than 40% in the diabetic patients [5, 6]. However, a recent systematic review showed that its total prevalence was 33.9% among Iranian people [7]. The detailed pathogenesis and etiology of the disease are still unknown [8–10]. Nevertheless, NAFLD may be associated with factors such as insulin resistance [10, 11], oxidative stress, and adipokines such as adiponectin, cytokines, and other inflammatory mediators [10, 12]. Insulin resistance increases lipolysis in adipose tissue, releases free fatty acids to liver, and causes inflammation in liver [10, 11]. Moreover, mitochondrial dysfunction, oxidative stress, and increased inflammatory responses are related to damaged liver [10, 12]. The low level of serum adiponectin was also observed in NAFLD patients, which was related to the rate of steatosis, fibrosis, and severity of NAFLD [13]. Since no definite treatment has been found for this disease, identification of new therapeutic approaches is one of the current challenges [10, 14, 15]. A study suggested that flavonoids such as anthocyanins, found in plant sources with red, purple, and blue colors [16] were effective in treating NAFLD [17]. According to the literature, the effects of anthocyanins on NAFLD include decrease of lipid accumulation in the liver [18–23], improvement of insulin resistance [24–27], decrease of lipid profile [23–26], inflammation [19, 26], and oxidative stress [28–32]. Moreover, some human studies reported useful effects of anthocyanins on the levels of liver enzymes such as ALT and AST [33, 34], oxidative stress markers such as MDA [35], inflammatory markers such as TNF-α [36, 37], lipid profile [35, 36, 38–40], glycemic control [38, 39], insulin resistance [40, 41] and adiponectin [41]. However, very few clinical trials evaluated the effect of anthocyanins [37, 42, 43] on NAFLD. For example, supplementation with purified anthocyanins for 12 weeks was associated with a significant decrease in the level of Alanine Aminotransferase (ALT) and cytokeratin-18 fragment M30 (CK-18 M30). However, it improved the fibrosis scores of NAFLD patients [42]. In addition, another research reported that intake of *Hibiscus sabdariffa* extract, rich in anthocyanins, for 12 weeks improved liver steatosis in patients with fatty liver [43]. A study found that consumption of bayberry juice, as a source of anthocyanins, for 4 weeks decreased the levels of TNF-α and CK-18 M30 among NAFLD patients [37]. Nevertheless, the earlier studies had various limitations: lack of precise examination of steatosis and fibrosis of liver by an accurate none-invasive method such as transient elastography (Fibroscan) [37, 42, 43], low study power [42], lack of assessing other important factors such as adipokines, adiponectin, as well as inflammatory and oxidative stress markers [37, 42, 43]. Recent evidences demonstrated that results of transient elastography, as a non-invasive method, had appropriate consistency with results of biopsy, as an invasive but gold standard method for assessing NAFLD. Therefore, transient elastography can replace biopsy as a more accurate and none-invasive method in evaluating NAFLD [44–46]. *Cornus mas* L. (cornelian cherry) is a fruit rich in anthocyanins [47]. Although its protective effects on liver was reported in several animal studies [48–51], no clinical trial has ever investigated the effect of cornelian cherry fruit extract on NAFLD. Considering the high prevalence of NAFLD as well as the limited number and limitations of clinical trials over the effect of anthocyanins on NAFLD, further clinical trials are required in this area. The future trials should conduct comprehensive investigations on important NAFLD variables and examine the impacts of anthocyanins on NAFLD. Therefore, the present double-blind randomized clinical trial will be conducted to investigate the effect of supplementation with total anthocyanin-base standardized cornelian cherry fruit extract on the liver function (Serum levels of AST, ALT and CK-18 M30; steatosis and fibrosis of liver), TNF-α, MDA, and adiponectin in patients with NAFLD. Furthermore, serum concentrations of glucose, total cholesterol (TC), High density lipoprotein (HDL-C), low density lipoprotein (LDL-C), triglyceride (TG), insulin, and insulin resistance will be evaluated as the secondary outcomes.

## Methods

### Design and aim study

This double-blind randomized parallel clinical trial will be carried out at the Department of nutrition, School of Public Health, Shahid Sadoughi University of Medical Sciences, Yazd, Iran. The main aim of this research is to investigate the effect of a 12-week supplementation with total anthocyanin-base standardized cornelian cherry fruit extract on liver function (Serum levels of AST, ALT and CK-18 M30; steatosis and fibrosis of liver), TNF-α, MDA, and adiponectin in patients with NAFLD. (Fig. 1 and Table 1). Moreover, serum concentrations of glucose, total TC, HDL-C, LDL-C, TG, insulin, and insulin resistance will be assessed as the secondary outcomes.

**Fig. 1 Fig1:**
[figure not shown]
Protocol flow diagram. We will perform a double-blind randomized clinical trial to evaluate the effect of total anthocyanin-base standardized (*Cornus mas* L.) fruit extract on the liver function, tumor necrosis factor α, malondealdehyde, and adiponectin in patients with non-alcoholic fatty liver

**Table 1 Tab1:** Study timeline; we predicted 20 months to carry out the present study

Description of research activity	Duration (month)																							
	1	2	3	4	5	6	7	8	9	10	11	12	13	14	15	16	17	18	19	20	21	22	23	24
Reviewing the literature and writing the proposal	*																							
Preparing the total anthocyanin-base standardized (*Cornus mas* L.) fruit extract and the placebo		*	*	*																				
Standardizing the extract based on the total anthocyanin					*																			
Selecting the participants						*	*	*	*	*	*													
Collecting data, conducting the intervention and assessments												*	*	*										
Entering the data into SPSS and conducting the statistical analysis															*	*	*							
Providing the final reports																		*	*	*				

The symbol * represents the start and end time of each research activity in study timeline

### Preparation of total anthocyanin-base standardized cornelian cherry fruit extract

#### Materials and extraction

Fresh ripe berries of cornelian cherry were prepared from the forests of Ghazvin, Iran, in October 2018 and frozen at − 18 ∘C. Later, the fruits’ authenticity will be determined by specifying their voucher number (SSU0029) in the Department of Pharmacognosy, School of Pharmacy, Shahid Sadoughi University of Medical Sciences, Yazd. In the next stage, the fruits will be cleaned and their cores will be removed. Then, the fruit samples will be grinded and mixed with the solvents including ethanol 80% and HCL 0.1%. Extraction will be performed by percolation for one week. Then, it will be followed by Ultrasound-Assisted Extraction (UAE) for 20 min using an ultrasonic device (Elmasonic Easy 60 H, German; frequency 50/60 Hz). After filtration of the obtained extract, it will be concentrated by evaporation.

#### Total anthocyanin content determination

The total anthocyanin content of the achieved extract will be determined using the pH differential method [52, 53].

Since the prepared extract does not have purified anthocyanins, the extract’s total flavonoid/phenolic content should be measured. Furthermore, the necessary microbiology measurements will be performed for the prepared extract.

#### Preparation of placebo

The placebo will be prepared using diluted water, caramel color, allura red color, and natural flavorings with a color, appearance, taste, and texture similar to the cornelian cherry extract, but without any anthocyanins.

### Study population

Patients with NAFLD will be selected based on the inclusion and exclusion criteria from gastroenterology clinics affiliated to Diabetes Research Center and Shahid Sadoughi University of Medical Sciences, Yazd, Iran. The inclusion criteria will be having 25–65 years of age; ALT levels of higher than 30 U/L in men and higher than 19 U/L in women; diagnosis of the disease by a gastroenterologist; and grade 1, 2, and 3 fatty liver. Furthermore, patients should be residents of Yazd city and will be required to sign the written consent forms to participate in the research. In the current research, nonalcoholic steatohepatitis (NASH) will be defined based on the guidelines of American Gastroenterological Association and American Association for the Study of Liver Diseases [54]. According to this guideline, NASH is defined as the presence of hepatic steatosis proved by ultrasonography or inflammation with hepatocyte injury (ballooning) with or without fibrosis [54]. Moreover, NAFLD will be diagnosed by ultrasonography based on following criteria: an increase in hepatic echogenicity via renal echogenicity as a reference, presence of enhancement and lack of differentiation of periportal, and bile duct walls reinforcement due to great hyperechogenicity of the parenchyma [55]. Exclusion criteria will include: having any history of diseases such as cirrhosis, viral hepatitis, cardiovascular disease, diabetes, Wilson, and cancer; taking medications including corticosteroids, non-steroidal anti-inflammatory drugs, hypoglycemic agents, or any medicines that affect the blood glucose, tamoxifen, sodium valproate, methotrexate, amiodarone, anti-retroviral agents for HIV, probiotics; consuming any medicine or supplement that affect liver function as well as supplements with antioxidant and anti-inflammatory properties (such as vitamin D, vitamin E, omega-3, resveratrol) one month before the study; following a special diet one month before the study; being pregnant and breastfeeding; and consuming alcohol. We will also ask the patients to not consume the medicines in exclusion criteria list during the study. Moreover, data of the patients with any of the following conditions will not be analyzed at the end of study: patients who take less than 80% of the administered extract or placebo as well as participants who are under a special treatment due to a specific medical reason during the study.

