### Sample size

To estimate the sample size, we considered 95% confidence interval; 80% power (α = 0.05 and β = 0.2); the changes of ALT levels in intervention group compared with the control group, and S = 24% to achieved the significance level of 16% in both study groups according to the study by Zhang et al. [42]. Therefore, the sample size was calculated as *n* = 36 for each group. Eventually, 40 patients will be recruited for each group considering the possible 10% loss.

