### Intervention

The target daily dose of 320 320 mg.d^− 1^ of total anthocyanin will be administered for 12 weeks [42]; with the required daily intake of extract adjusted in accordance with the total anthocyanin content measured in the extract. Moreover, the total anthocyanin content in the extract will be measured in distinct intervals during the trial (on days 1, 6, 12, 20, and after 6 months). If it is required, we will adjust the amount of consumed extract based on its total anthocyanin content.

The control group will also receive the placebo, matched with the extract in terms of appearance, taste, color, and texture (but without any anthocyanins) for 12 weeks. The participants will be asked to keep the intervention and placebo, which are presented as liquid in the refrigerator to ensure food safety.

In the current double-blind randomized clinical trial, the cornelian cherry extract and the placebo will be packed in containers with the same color, shape, and size, so that they cannot be identifiable by the patients or administrators. A person out of research, who does not know about the details of study, will be asked to label the bottles containing the extract or placebo as A or B, the contents of these bottles should be consumed in one month by participants. This person will be asked to inform the researchers about his/her labeling selection at the end of study. We will also ask the participants to give back their bottles (empty or not) at the end of each month and receive the next bottles until the end of study. At the end of intervention, the remaining contents of bottles will be recorded for each participant. Moreover, regular consumption of the extract or placebo will be checked by contacting the patients during the survey. At the end of the trial, the consumed amounts of extract or placebo will be estimated considering the remaining contents of the bottles for each participant. In the case that a patient in each group consumed less than 80% of the administered extract or placebo, his/her data will not be analyzed at the end of the study.

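### Randomised patients are dropped from the analysis for low intake or other treatment during the study, so the stated comparison is not protected by randomisation; the same exclusions draw on the 10% loss allowance

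*Protocol article*

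**What the plan says.** The rule stands in two places in the protocol article. At the end of *Study population*, the patients whose data will not be analysed are listed as "patients who take less than 80% of the administered extract or placebo as well as participants who are under a special treatment" for a medical reason during the study. The *Intervention* section repeats the adherence half for either group: if a patient "consumed less than 80% of the administered extract or placebo, his/her data will not be analyzed at the end of the study". Intake is worked out from what remains in the returned bottles, so it is known only after assignment.

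*Statistical analysis* lists t-tests, Mann-Whitney and Wilcoxon tests, and an ANCOVA of post-intervention values adjusted for baseline and covariates. It names no analysis set. The restricted set is therefore the only one the article describes.

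*Sample size* gives 36 per group and then an allowance: "Eventually, 40 patients will be recruited for each group considering the possible 10% loss". It does not say whether that loss includes the patients removed by the two rules, and it gives no expected rate for either.

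**The concern.** Randomisation makes the two groups comparable as assigned. It does not make the adherent, otherwise untreated parts of those groups comparable. Intake over 12 weeks can depend on which product a patient was given and on how the patient is doing. The same is true of starting another treatment: someone treated because of deterioration would be removed, and a poor outcome would go with them. If this happens more in one arm, or to different kinds of patient in the two arms, part of any difference in ALT or the other outcomes reflects who was removed. Baseline adjustment cannot fully repair this, because the causes arise after baseline. The rule applies to every between-group comparison in the trial.

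A smaller, separate matter is the planned number analysed. Ordinary dropout and the two exclusion rules together must fit within the margin between 36 and 40 if the design power is to be kept.

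**Working it through.** **1. The plan's own figures.** Inputs from *Sample size*: "80% power (α = 0.05 and β = 0.2"; SD 24%; and 16%, which the text calls a significance level but which works only as the difference to detect. Two-sided testing is assumed, in line with the 95% confidence interval.

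- n per group = 2 × [24 × (1.960 + 0.842) / 16]² = 35.3, rounded up to 36. This reproduces the plan.
- 36 / (1 − 0.10) = 40. This also reproduces the plan.
- The margin is 40 − 36 = 4 patients per group, with none spare.

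**2. Bias from exclusion (illustration).** The protocol gives no rates, so these are assumptions: p1 = 0.15 excluded on extract, p0 = 0.05 on placebo, and excluded patients worse by δ = 0.5 to 1.0 SD in both arms. The formula depends on what *worse* is measured against.

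- Against the retained patients of the same arm: bias = δ × (p1 − p0) = δ × 0.10.
- Against the mean of the whole arm: bias = δ × [p1/(1 − p1) − p0/(1 − p0)] = δ × (0.1765 − 0.0526) = δ × 0.1238.

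Points are SD × 24. The false-favourable rate is the upper tail of a two-sided 5% t-test by the noncentral t, with 34 and 38 analysed (40 × 0.85 and 40 × 0.95) and no true effect.

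| δ | Reference | Bias (SD) | ALT points | Share of 16 | False result favouring extract | Total two-sided error |
|---|---|---|---|---|---|---|
| 0.5 | retained | 0.050 | 1.2 | 7.5% | 4.0% | 5.5% |
| 0.5 | whole arm | 0.062 | 1.5 | 9.3% | 4.4% | 5.8% |
| 1.0 | retained | 0.100 | 2.4 | 15% | 6.2% | 7.0% |
| 1.0 | whole arm | 0.124 | 3.0 | 18.6% | 7.5% | 8.1% |

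Without bias the favourable tail is 2.5% and the total is 5%. If p1 = p0 and δ is the same in both arms, both formulas give zero. If the heavier exclusion fell on placebo, the sign would reverse.

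**3. Power under total loss** (dropout plus exclusions; rates assumed; difference 16, SD 24, noncentral t).

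| Total loss | Analysed per arm | Power |
|---|---|---|
| 10% | 36 | 79.7% |
| 15% | 34 | 77.3% |
| 20% | 32 | 74.7% |
| 30% | 28 | 68.8% |

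In the 15%/5% scenario alone, 34 + 38 = 72 are analysed, the same total as 2 × 36, and power is 79.5%.

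**4. Power if everyone is analysed as assigned.** Assume 10% of patients show no effect, so the mean difference is 16 × 0.9 = 14.4. Power is about 75.5% with 40 per arm and about 71% with 36.

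**The case against.** Several points on the other side are fair.

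- **The allowance.** A reader might infer that the exclusions exhaust the 10%. The documents do not support that. No exclusion rate is given, *loss* is not defined and may already include these patients, and the 15%/5% illustration leaves the planned total of 72. What stands is that the exclusions draw on a margin of four per arm.
- **Unequal tolerability.** A reader might infer that the extract is acidified and so harder to take than the placebo. The acid appears only in the extraction solvent, before filtration and evaporation. The placebo is described as matched in taste, colour and texture, and the containers are identical. Differential exclusion is possible but not shown.
- **Size.** The illustration runs in one direction, and balanced exclusion gives no bias. Stratification by severity and the baseline-adjusted ANCOVA may remove the part of an imbalance that baseline explains, but not the part due to later events.
- **A condensed article.** A full analysis plan may exist, and an unnamed analysis set would not by itself be a finding. But the exclusion is stated outright, and for adherence it is stated twice. A plan that analysed everyone would contradict this text.
- **Power.** Analysing everyone dilutes the effect, so power is no argument for the change. That stands in full.

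**Conclusion.** The concern holds as a matter of bias. The article fixes an analysis that removes randomised patients on post-randomisation conditions and describes no as-randomised analysis beside it. The comparison it states is therefore open to bias whenever exclusions differ by arm in number or prognosis.

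Nothing in the documents shows how large that bias would be. The 1.2 to 3.0 points, and the 4.0% to 7.5% chance of a false result favouring the extract, rest entirely on the assumed 15%/5% exclusion and 0.5 to 1.0 SD worse prognosis. The lower figures take retained patients as the reference and the higher ones the whole arm. The defect does not depend on these figures, because it lies in the rule.

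The allowance is a secondary point. The figures 36 and 40 are correct, four patients per arm is the whole margin, and the text should say whether rule-based exclusions come out of it. It does not follow that the trial is underpowered.

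**What to change.** Replace the exclusion sentences in *Study population* and *Intervention*, and make these changes:

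1. The primary analysis compares all randomised patients in the group to which they were assigned, whatever their adherence or concomitant treatment, using the baseline-adjusted ANCOVA already planned.
2. Week-12 samples are sought from every patient, including those who have stopped the product.
3. Missing week-12 outcomes are handled by a stated method, for example multiple imputation using baseline values and arm, with a sensitivity analysis of its assumptions.
4. The set with at least 80% intake is reported as a sensitivity analysis.
5. *Sample size* states that the 10% covers missing week-12 outcomes.

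The cost is revised wording plus the effort of keeping the week-12 visit for patients who stop. This should be settled before follow-up ends, because samples not taken at week 12 cannot be recovered. The downside is dilution by non-adherence: with 10% of patients showing no effect, power is about 75% at 40 per arm and 71% at 36. If the sponsor wants 80% power for the as-assigned effect, the sample size needs its own assumption about non-adherence.

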### Ethical considerations and trial registration

This survey was approved by Ethics Committee of Shahid Sadoughi University of Medical Sciences, Yazd, Iran (approval number: IR.SSU.SPH.REC.1396.171). The research was also registered on Iranian Registry of Clinical Trials (IRCT registration code: IRCT20180419039359N1). After informing the participants about the study protocol, they will be asked to sign the informed consent forms.

### Sample size

To estimate the sample size, we considered 95% confidence interval; 80% power (α = 0.05 and β = 0.2); the changes of ALT levels in intervention group compared with the control group, and S = 24% to achieved the significance level of 16% in both study groups according to the study by Zhang et al. [42]. Therefore, the sample size was calculated as *n* = 36 for each group. Eventually, 40 patients will be recruited for each group considering the possible 10% loss.

